#### 1.4.2 Choice of main judgement criterion

The interest of such drugs and their place in the therapeutic strategy of COVID-19 must be judged on a clinical criterion and not only on the evolution of the virological test. We have retained as the main judgement criterion that of “hospitalisation or death”. Criteria justifying hospitalisation for COVID-19 shall be standardised and follow current recommendations. This reliable criterion allows an evaluation of the efficacy of early-stage, outpatient treatments.

#### 1.4.3 Choice of treatments

Among people aged over 65 staying at home, treatments must be acknowledged as being well tolerated and not posing drug interaction problems prohibiting their use with very many people.

For the start of the trial, we have therefore retained hydroxychloroquine, favipiravir, telmisartan and imatinib, which seem to present currently *a priori* the best tolerance profile within this population.

We have neither retained lopinavir/ritonavir, entailing too many digestive problems, nor darunavir/ritonavir nor darunavir/cobicistat, which would be better tolerated, but would lead to too many people being discarded on grounds of possible drug interaction problems.

Hydroxychloroquine has been retained as an experimental treatment, not as a benchmark treatment. The researchers for this trial have monitored the controversy, generated as much by the media as the science regarding the efficacy of hydroxychloroquine. Scientifically, there exists limited and contradictory data and no evidence of its clinical efficacy in this indication. At the media level, it is actually possible that the scale of this controversy could render the testing model incomprehensible for the target population. If that were the case, the researchers would seek recommendations of the SAB regarding the necessary changes to the trial model. In such a situation, the hydroxychloroquine arm could become the new control arm (in the absence of convincing evidence of efficacy), thus the relevance of the trial would be reduced. With consideration to the multi-arm model, a difference between hydroxychloroquine and one or the other of the experimental treatments would allow conclusions to be drawn on what would be the meaning of such a difference. Any absence of difference, however, would not be very informative and not allow any conclusions.

Within this population, the issue of multiple drug treatments, with their risks of interaction, cardiac toxicity induced by chloroquine and its derivatives, will be the subject of particular attention. ECG shall be systematic before inclusion, opinion from a cardiologist would be sought in cases of doubt and people included, yet considered as needing to be monitored on this point, would be provided with a self-monitoring ECG device with remote transmission.

#### 1.4.4 Choice of studied population

As for all antiviral treatments, treatment for SARS-CoV-2 would have more chance of being efficacious, if it were administered as quickly as possible after symptoms onset. We have retained as an inclusion criterion “having experienced symptoms for fewer than 72 hours at the time of diagnostic testing”.

The main group of the main trial shall be made up of people not taking renin-angiotensin system blockers (ACEI or ARB) before inclusion, who would be randomised between the 5 arms of the study. Calculations for the scale of the study allow for the necessary ability to make comparisons within this group.

People taking renin-angiotensin system blockers (ACEI or ARB) before inclusion represent approximately 20% of patients of the target population for which the study shall be proposed. They cannot be randomised in the Telmisartan arm, but we did not wish to exclude them from the study. They shall therefore be randomised into the 4 other arms and constitute a separate group, which shall be analysed independently. The scale of the study within this group is based on the feasibility of recruitment, using the calculation of the scale of the study of the main group. An extension of the scale

of the study could be made after opinion from the SAB to allow sufficient statistical significance within this group. If the Telmisartan arm of the main group is abandoned in the course of the study on grounds of futility, then people taking renin-angiotensin system blockers (ACEI or ARB) are able to be randomised in the main trial.

## 2 PRIOR PROJECTS OF THE TEAM

[name], coordinating investigator of this project, is the head of the tropical and traveller's diseases clinic at "CHU de Bordeaux". He has implemented and supervised the treatment of suspected or confirmed cases of COVID19 since the start of the epidemic. He is affiliated to the Inserm 1219 Research Centre – IDLIC team at the University of Bordeaux. Within the IDLIC team, he leads the project of "infectious diseases with considerable epidemiological potential", which notably works on viral haemorrhagic fevers. In this regard, he has successfully implemented therapeutic trials and cohort studies in contexts of extreme urgency and logistical challenges during the Ebola epidemic in Guinea in 2014-2015 and the Lassa Fever epidemic in Nigeria in 2018, 2019 and 2020 (51,62,63). The IDLIC team has 25 years of experience in large-scale international therapeutic trials (64) and is in a position to implement a trial on COVID-19 very rapidly. It has available a network of partners across the world, as it is currently coordinating 22 studies occurring in 23 countries (South Africa, Benin, Brazil, Burkina Faso, Cambodia, Cameroon, Ivory Coast, Gambia, Ghana, Guinea, Guinea-Bissau, Madagascar, Mali, Mozambique, Niger, Nigeria, Uganda, Central African Republic, Democratic Republic of Congo, Senegal, Tanzania, Togo and Vietnam). This network can be mobilised very rapidly, as it is currently working on several other communal, multi-site studies. For this study, the IDLIC team will draw from the clinical trials platform, EUCLID/F-CRIN (CIC1401, Bordeaux). This platform is a consortium of Inserm, the CHUs of Bordeaux and Limoges, the University of Bordeaux and the Bergonié Institute of Bordeaux, bringing together expertise in clinical research of the teams from these institutions. EUCLID is one of the clinical trial platforms selected by a call for tenders by F-CRIN (national infrastructure for biology and health, founded in the context of the French future stimulus plan). EUCLID has also been awarded the label "Research Platform for the University of Bordeaux" (2019) and "ECRIN Data Centre" (2015). EUCLID covers all activities required for complex or international academic clinical trials at all stages of clinical development, in collaboration with the sponsor and the coordinating researcher. Since its creation, the platform has undertaken nineteen projects, of which the majority are complex or international trials in the field of infectious diseases.

## 3 OBJECTIVES

### 3.1 Main objective

The study's main objective is to appraise the efficacy of several specific experimental treatments, compared with standard of care, to avoid hospitalisation or death on Day 14 among adults older than 65, suffering from symptomatic infection by SARS-CoV-2, presenting symptoms for fewer than 72 hours at the time of testing and having no hospitalisation criterion.

### 3.2 Secondary objectives

The study's secondary objectives are:

- Appraise the efficacy of several experimental treatments of SARS-CoV-2 infection, compared with standard of care, to prevent death on Day 28
- Appraise the efficacy of several experimental treatments of SARS-CoV-2 infection, compared with standard of care, to prevent hospitalisation on Day 28
- Appraise the efficacy of several experimental treatments of SARS-CoV-2 infection, compared with standard of care, to prevent admission to intensive care unit on Day 28
- Appraise the efficacy of several experimental treatments of SARS-CoV-2 infection to eliminate nasopharyngeal carriage of the virus, compared with standard of care
- Appraise the efficacy of several experimental treatments of SARS-CoV-2 infection, compared with standard of care, to prevent loss of autonomy
- Appraise tolerance of experimental treatments against SARS-CoV-2 infection
- Study those factors associated with clinical deterioration in patients with COVID-19
- Evaluate the feasibility and acceptability of the trial and model of care model implemented.
- Evaluate the relationship between concentrations for each drug and efficacy of each of the treatments

## 4 Trial model

### 4.1 Study phase and classification

This study is seamless phase II/III, multicentre, multi-stages and with multiple parallel arms (MAMS), controlled, randomised, superiority clinical trial.

### 4.2 Groups of treatments

The participants are randomised, in a ratio of 1:1 in each arm, according to the following strategies:

- Arm 1: Treated under standard of care (control arm).
- Arm 2 to X: Experimental treatment (one per arm, X being the number of arms)

#### 4.2.1 Choice of treatments at the time of drafting the protocol

At the time of drafting this protocol:

- The people of the control arm shall receive a food supplement (AZINC Forme et Vitalité®) containing a complex of vitamins and trace elements, for which there is no reason to believe that they are active on the virus.
- Those experimental treatments retained are
  - hydroxychloroquine, favipiravir, imatinib and telmisartan, for people who were not taking renin-angiotensin system blockers (ACEI or ARB) before inclusion.
  - hydroxychloroquine, favipiravir and imatinib, for people who were under treatment by renin-angiotensin system blockers (ACEI or ARB) before inclusion.

#### 4.2.2 Evolution in the choice of treatments

All changes to the treatment arms must be approved by the SAB for the trial and be the subject of an amendment, which is submitted to the ethical and regulatory authorities.

This change, which is authorised by the trial model and foreseen within the randomisation procedures, could have two triggers: (i) the scope of the controversy about hydroxychloroquine in the media; and (ii) new scientific findings emerging from the trial's intermediate analyses or from external studies, providing evidence of efficacy for one of the treatments.

Once the trial has started:

- If any experimental treatment proves to be efficacious before the end of the trial (via external data or a major sign of efficacy in the trial), the opinion of the DSMB shall be urgently sought and the design adapted to this new context.
- Groups which are experimental shall be interrupted prematurely if the efficacy or futility criteria are fulfilled before the end of the trial, or if the DSMB considers that safety has not been assured.
- New experimental groups can be added, if new evidence suggest that other treatments should be tested.

### 4.3 Judgement criteria

#### 4.3.1 Main criterion

The main criterion shall be the proportion of participants with an occurrence of hospitalisation and/or death between Day 0 and Day 14 in each arm.

All hospitalisations shall be taken into account, whatever may be their reason. Hospitalisation criteria, however, shall be standardised and specified in a specific procedure [SDPM].

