## 5 METHODS

### 5.1 Eligibility criteria

#### 5.1.1 Inclusion criteria

- Positive test for SARS-CoV-2 on a nasopharyngeal swab
- Appearance of symptoms <72 hours before taking the nasopharyngeal swab
- Age  $\geq 65$
- Valid person, ambulatory, with full capacity to understand the challenges of the trial
- No hospitalisation criteria according to current guidelines
- Signed, informed consent

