#### 5.1.2 Non-inclusion criteria

##### 5.1.2.1 Autonomy

- Incapable of understanding the meaning of participating in the study (*i.e.*: dementia) or to make a decision to participate (*i.e.*: person under protection of justice, tutorship or guardianship).
- Person with a score  $\geq 7$  on the Rockwood Clinical Frailty Scale
- Chronic illness at a severe stage, with limited life expectancy.

In the particular case of people resident in a nursing home, opinion on inclusion from the coordinating physician of the facility shall be sought, with particular consideration to the environment and the practices at the nursing home.

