#### 5.4.3.2 Immediate notification of serious adverse events (SAEs) and new findings

The researcher is to evaluate each adverse event with regard to its seriousness.

The researcher must notify the Safety and Monitoring Unit by fax, email or via the eCRF [SDPM], **immediately** from the day of becoming aware of it, of all SAEs and all new findings, with the exception of the following SAEs:

- Pre-existing or documented pathology before the signature of consent to the trial and remaining at a degree of severity equal or lesser than that preceding the initial treatment of the trial.
- Hospitalisation for medical or surgical treatment scheduled before the research;

If the researcher becomes aware of a Serious Adverse Event, for which he suspects a causal link with the research, occurring after the end of research for any participant whom he has treated, he is to inform the Safety and Monitoring Unit immediately.

**The researcher must document the event to the best of his ability, providing, if possible, the medical diagnosis.** The researcher must satisfy himself that information relevant to the follow-up has been communicated to the Safety and Monitoring Unit as soon as possible.

The researcher must send on, in addition to the form for notifying SAEs, copies of the laboratory results or examination or hospitalisation reports, giving details of the Serious Adverse Event, including the relevant negative results **without omitting to anonymise these documents** and include the participant's number and code before sending.

**The researcher must monitor the participant having presented with an SAE until its resolution, stabilisation at a level judged by him as medically acceptable or the previous state resuming, even if the participant has stopped the research's procedure.** Any addition to the information pertaining the changes in the event, if it has not been mentioned in the first report, shall be sent to the Safety and Monitoring Unit by the researcher.

All Serious Adverse Events, for which the researcher or the Safety and Monitoring Unit deems that a causal relationship could plausibly be foreseen, are to be considered as suspicions of Serious Adverse Reactions.

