## 6.2 Sample Size

### 6.2.1 Participants not taking ACEI or ARB before inclusion

The incidence assumptions on primary endpoint are based on extrapolations from aggregated data published in other contexts thus far. The DSMB will check these assumptions and recommend a sample size revision, if needed.

We assumed that the proportion of participants reaching the primary endpoint at D14 in the control arm could be up to 25%. An experimental treatment will be deemed efficient if this proportion is reduced by at least one half. We also considered a power of 80% for all tests.

Three futility (interim) analyses will be performed successively. We defined successive arm discontinuation thresholds for the one-way first type error alpha using STATA package NStageBin for conception and sample size of MAMS trials (65,66).

Two efficacy analyses (interim n°3 and primary) will be performed successively. We will use the O'Brien & Fleming procedure to define the first type error alpha for each analysis, based on the data observed at the first futility analyses (67,68).

Sensitivity analysis at D28 will be exploratory only, without impact on sample size.

Tests of difference between arms will be one-sided. Arm discontinuation thresholds and sample size for each analysis are given here below:

| Analysis    | Trigger
Number of participants in the control arm having reached D14 | Objectives     | Alpha           |
|-------------|-------------------------------------------------------------------------|----------------|-----------------|
| Interim n°1 | 30                                                                      | Futility       | 0,65            |
| Interim n°2 | 60                                                                      | Futility       | 0,45            |
| Interim n°3 | 102                                                                     | Futility       | 0,25            |
|             |                                                                         | Early efficacy | O'Brien-Fleming |
| Primary     | 169                                                                     | Efficacy       | O'Brien-Fleming |
| Sensitivity | End of trial                                                            | Efficacy       | 0,05            |

The sample size required is 169 participants by arm (845 overall). Since the "Missing as failure" procedure is used, there is no need to increase sample size to account for missing data.

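### A hospital stay booked before inclusion and falling by Day 14 counts as a primary failure, and no eligibility criterion removes it: a minor dilution that one line would prevent

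*Protocol*

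**What the plan says.** Section 4.3.1 defines the primary endpoint as "the proportion of participants with an occurrence of hospitalisation and/or death between Day 0 and Day 14 in each arm". It then says "All hospitalisations shall be taken into account, whatever may be their reason", followed by "Hospitalisation criteria, however, shall be standardised and specified in a specific procedure". The footnote to that sentence gives the criteria currently proposed: oxygen saturation, respiratory rate, heart rate, blood pressure, and the attending physician's judgement.

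On eligibility, the only inclusion item that touches hospitalisation is "No hospitalisation criteria according to current guidelines" (5.1.1). This concerns clinical need at inclusion. The non-inclusion lists (5.1.2.1 to 5.1.2.4 and the Summary) cover autonomy, cardiac risk, medicines and medical history. The broadest item on other illness is "Chronic illness at a severe stage, with limited life expectancy" (5.1.2.1). None mentions a planned admission.

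Section 5.4.3.2 does mention planned admissions. Among the SAEs that need no immediate notification it lists "Hospitalisation for medical or surgical treatment scheduled before the research".

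On size, section 6.2.1 says "We assumed that the proportion of participants reaching the primary endpoint at D14 in the control arm could be up to 25" per cent, and "An experimental treatment will be deemed efficient if this proportion is reduced by at least one half". It states 80% power, one-sided tests and 169 participants per arm, with no inflation.

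**The concern.** The participants are aged 65 or over. Some may have elective surgery, an investigation or a course of hospital treatment booked within two weeks of inclusion. Under sections 4.3.1 and 5.1 such a person can be enrolled, and the stay is a primary event if it goes ahead.

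The trial aims to avoid clinical deterioration (1.1), and hospitalisation or death was chosen as a clinical measure of drug efficacy (1.4.2). An admission fixed before randomisation says nothing about either. It adds the same expected number of events to each arm, pulls the risk ratio towards 1, lowers power, and makes it slightly more likely that an effective arm is stopped at one of the three futility looks.

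**Working it through.** **Inputs from section 6.2.1.** Control risk 25%; experimental risk 12.5% (halved); 169 per arm; futility thresholds 0.65, 0.45 and 0.25 (one-sided) at 30, 60 and 102 per arm; O'Brien-Fleming efficacy tests at 102 and 169. The overall efficacy level is not given as a number.

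**Reproducing 169.** For a single two-proportion test at 80% power:
- one-sided 0.05: 120 per arm (136 with continuity correction);
- one-sided 0.025: 152 per arm (168 with continuity correction).

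Simulating the four-stage design (300,000 runs, Lan-DeMets O'Brien-Fleming spending, pooled two-proportion z-test) at 169 per arm gives 80.1% power at overall one-sided 0.025 and 85.0% at 0.05. The stated 80% therefore matches 0.025, which is used below.

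**Adding booked stays.** Let q be the share of each arm with a booked stay that goes ahead by Day 14. This is an assumption; the protocol gives no figure. Each such person has an event in either arm, and the drug halves the risk in everyone else.

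*Case 1: booked stays come on top of the 25%.* The risk is q + (1 − q)p.
- q = 1%: control 0.01 + 0.99 × 0.25 = 25.75%; experimental 0.01 + 0.99 × 0.125 = 13.4%; risk ratio 0.52.
- q = 2%: 26.5% against 14.25%; risk ratio 0.54.

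*Case 2: booked stays are already inside the 25%.* Control stays at 25%. Experimental is q + (0.25 − q)/2 = 0.125 + q/2.
- q = 1%: 13.0%, a relative reduction of 48%.
- q = 2%: 13.5%, a relative reduction of 46%.

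**Power at 169 per arm, four-stage design, one-sided 0.025**

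| q | Case 1 | Case 2 |
|---|---|---|
| 0 | 80.1% | 80.1% |
| 0.5% | 79.3% | 78.5% |
| 1% | 78.2% | 76.5% |
| 2% | 76.2% | 72.5% |

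At overall one-sided 0.05 the starting point is 85.0%. It falls to 83.5% (Case 1) or 82.3% (Case 2) at q = 1%, and to 81.9% or 79.1% at q = 2%.

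**Chance that a truly halving arm is dropped for futility at any of the three looks**
- Case 1: about 9.8% at q = 0, then 10.3%, 10.7% and 11.6% at q = 0.5%, 1% and 2%.
- Case 2: about 11.5% at q = 1% and 13.2% at q = 2%.

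**Equivalent sample size** (single test, one-sided 0.025). From 152 per arm, Case 1 needs 161 at q = 1% and 169 at q = 2%; Case 2 needs 167 and 184.

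**Type I error.** If a drug does nothing, both arms have the same risk whatever q is, so the test keeps its level.

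**The case against.** **The all-cause count is deliberate.** In an open-label trial it avoids unblinded judgement of why someone was admitted. This stands, and it is a reason to act on eligibility rather than on the endpoint.

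**The hospitalisation procedure is not shown and might deal with scheduled stays.** That is possible. As written, though, the sentence and its footnote govern when to admit, while the sentence before them counts every stay.

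**q is assumed and is probably small.** This stands. Participants have a positive swab and symptoms of under 72 hours, hospitals are described as overwhelmed (Summary), and confinement of the population is anticipated (5.3.9). Many booked stays would be postponed.

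**There are partial safeguards.** The DSMB will check the incidence assumptions and may recommend a new sample size (6.2.1). Causes of hospitalisation are collected to Day 28 (4.3.2), so planned stays might be identified afterwards. Neither keeps these events out of the primary analysis.

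A reader might infer two stronger points that the documents do not support:

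- *That the protocol contradicts itself by treating one stay as an efficacy failure and a safety non-event.* Section 5.4.3.2 waives only immediate notification and still classes such stays as SAEs, and 5.4.3.1 requires all adverse events to be reported. A notification rule and an efficacy endpoint serve different purposes. The waiver shows only that planned stays were foreseen.
- *That knowledge of the arm will decide whether a booked stay is kept or postponed, and so bias the comparison.* This is conceivable in an open-label trial, but nothing in the protocol indicates it, and the calculation above does not rest on it.

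**Conclusion.** The point holds as a minor, avoidable weakness. As written, a stay booked before inclusion that takes place by Day 14 is a primary failure beyond the reach of any treatment. At q = 1% the cost is about 2 points of power (80.1% to 78.2%) if booked stays add to the 25%, and about 4 points (to 76.5%) if they are already inside it. The chance of wrongly dropping an effective arm rises by about 1 to 2 points. At q = 0.5% the power loss is under 2 points either way.

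These figures assume an overall one-sided level of 0.025, a drug that halves the risk in everyone without a booked stay, and booked stays that go ahead equally in all arms. The loss becomes material only if booked stays are more common than the setting suggests. The validity of the test is not in question.

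**What to change.** Add one non-inclusion criterion to section 5.1.2 and the Summary: *hospital stay already scheduled between Day 0 and Day 14*. Check it at the inclusion visit before randomisation, alongside the existing review of current treatments (5.3.3). Leave the all-cause count in 4.3.1 as it stands. The cost is one line and one question; a few otherwise eligible people would not be enrolled.

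If exclusion is not wanted, record booked stays before randomisation and use that record only in a sensitivity analysis of the primary endpoint. It should not become an exception within the primary endpoint. Such a rule would need a decision, after allocation and by staff who know the arm, on whether a stay had been brought forward or prolonged. That would reopen the judgement of cause that the all-cause count avoids.
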